Patients will be excluded if they fail to attend scheduled telerehabilitation sessions or respond to WhatsApp communication. Those experiencing unexpected medical complications, such as infections or cardiac or respiratory events, will be instructed to discontinue the program and withdraw from the study. The exclusion criteria also included changes in clinical status leading to surgical contraindications or new injuries during the prehabilitation period that prevented participation in home exercises. Additionally, participants with cognitive deficits were excluded based on the Portuguese version of the Mini-Mental State Examination (MMSE), with cut-off scores of ≤20 for illiterate individuals, ≤25 for primary school level, ≤26.5 for junior high school, ≤28 for high school, and ≤29 for higher education [15].

Randomization

After the explanatory meeting, eligible participants who complete baseline assessments will be randomized using simple randomization with a 1:1 allocation ratio via Randomizer® (www.randomizer.org). The allocation sequence will be generated by an independent researcher not involved in enrollment or assessment. Allocation concealment will be ensured using sequentially numbered, opaque, sealed envelopes, which will be opened only after confirming participant eligibility.

Control group

The participants in the control group will receive an institutional educational booklet containing standard preoperative physiotherapy recommendations. The only exercise instructions before TKA provided in the booklet were as follows: “(1) Move your feet up and down 20 times (active movement while lying on a treatment table, plantar dorsiflexion) and (2) inhale deeply through your nose while raising your arms and exhale through your mouth as you lower them. Perform 20 repetitions.” Participants in the control group will only follow these institutional procedures and will not engage in a home-based program. They will be instructed to maintain their usual daily activities and adhere to the recommendations provided in the booklet.

Experimental group

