Patients in the experimental group will receive the institutional booklet and participate in a semi-supervised home-based prehabilitation program. Before starting, they will undergo theoretical and practical instruction to ensure proper exercise execution, as outlined in Table 1. Additional time will be allocated during the initial phase to overcome individual digital barriers, and all participants in the intervention group will receive in-person training on how to access video calls, send messages, and interact with the WhatsApp platform. The research team will verify movement accuracy, provide guidance to family members for additional support, and monitor any changes in the participants' physical or mental conditions. The training protocol was designed for a home setting without the need for specialized equipment and was adapted from the tele-prehabilitation model proposed by Guida et al. [16]. It consists of (1) warm-up, (2) balance exercises, and (3) muscle strengthening exercises. Sessions will be conducted three times per week over eight weeks, with at least 48 hours of rest between sessions, totaling a maximum of 24 training sessions.

**Table 1 TAB1:** Home-based exercise protocol. *Estimated time.

	Exercise	Sets	Repetitions	Rest	Time*
Warm-up					
	Seated knee flexion and extension	3	10 movements per leg	No rest	2 min
	Marching in place	3	30 movements	30 s	4 min
Balance					
	Single-leg stance	3	15 s per side	30 s	3 min
	Tandem walking (heel-to-toe)	3	10 steps in each direction	30 s	5 min
Strength					
	Sit-to-stand	3	10	30 s	5 min
	Wall calf raises	3	10	30 s	5 min

To enhance adherence and technique, participants will receive a link to an instructional video (Video 1) and a training diary to log their weekly exercise frequency (Table 2 of Appendices). Additionally, weekly videoconference sessions provide real-time feedback, while WhatsApp monitoring facilitates communication, allowing participants to ask questions via text, images, audio, or video messages. WhatsApp was selected because of its accessibility and ease of use. To further minimize attrition, the research team will send daily reminder messages via WhatsApp each morning, reinforcing engagement. Weekly live video calls will also serve to optimize exercise execution and encourage adherence.

**Video 1 VID1:** Instructional video demonstrating proper exercise techniques for patients in the home-based prehabilitation program.

Primary outcome

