Adherence to the prehabilitation program will be assessed by calculating the percentage of completed sets compared to the total prescribed sets. This information will be recorded in the training diary and reported by the patient or a family member. The number and classification of adverse events occurring during the home-based training period will be recorded separately from hospital outcomes.

Adherence will be operationally defined as the completion of ≥75% of prescribed sessions, based on adherence rates commonly reported in the literature. A recent systematic review by Adebero et al. [7] found that most prehabilitation trials achieved adherence rates of 74% or higher, supporting the use of this threshold. This cutoff will be used to determine eligibility for per-protocol analyses evaluating intervention efficacy, while all randomized participants will be retained in the dose-response analysis, regardless of adherence level.

Hospital outcomes

Hospital outcomes will include the length of hospital stay (in days), hospital readmission rate, and number and classification of complications occurring within 30 days post-surgery. These indicators were selected to complement the biological and functional recovery metrics, offering system-level proxies for early recovery quality. Specifically, reduced length of stay may reflect improved physiological readiness for discharge, while lower readmission and complication rates may signal enhanced resilience and postoperative recovery. These data will be retrieved from patients’ medical records, which will be accessed using the registration number recorded during patient enrollment. Surgical complications will be defined as any adverse events based on the Clavien-Dindo classification [26].

Satisfaction level

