Missing data will be addressed using linear regression models to examine the dose-response relationship, including participants who did not reach the ≥75% adherence threshold as well as those who withdrew from the intervention due to comorbidities or frailty. These individuals will be retained in the analysis to reflect real-world variability.

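### Exclusion for missed telerehabilitation sessions or unanswered WhatsApp messages acts after randomisation, falls on the experimental arm, and conflicts with the stated retention of low adherers

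*Protocol article*

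**What the plan says.** Under Randomization, allocation follows the baseline visit: "eligible participants who complete baseline assessments will be randomized using simple randomization with a 1:1 allocation ratio". Envelopes are opened once eligibility is confirmed.

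Under Enrollment, the exclusion paragraph nevertheless lists events that come later:

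- Non-attendance and non-response: "Patients will be excluded if they fail to attend scheduled telerehabilitation sessions or respond to WhatsApp communication". No number of sessions or messages is given.
- Unexpected medical complications: these patients "will be instructed to discontinue the program and withdraw from the study".
- A change in clinical status that contraindicates surgery, or "new injuries during the prehabilitation period that prevented participation in home exercises".

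On who is exposed to the programme, the Control group section states: "Participants in the control group will only follow these institutional procedures and will not engage in a home-based program". The Experimental group section adds that "all participants in the intervention group will receive in-person training on how to access video calls, send messages, and interact with the WhatsApp platform". Weekly video sessions, WhatsApp monitoring and daily reminders are also described only there.

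On retention, Prehabilitation adherence uses completion of at least 75% of sessions to decide per-protocol eligibility and says that "all randomized participants will be retained in the dose-response analysis, regardless of adherence level". The last paragraph of Results refers to participants below 75% and to those who left the intervention because of comorbidities or frailty: "These individuals will be retained in the analysis to reflect real-world variability".

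**The concern.** An exclusion criterion protects the comparison only if it is applied before allocation. One that depends on how a patient behaves in a programme offered to one arm is applied to that arm alone. The patients it removes are likely to be the less engaged and, through the medical and injury clauses, the less well. The remaining experimental patients would then be compared with an unselected control arm.

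The consequence depends on whether engagement or health is related to the outcome. For CRP a link is plausible: the Primary outcome section itself names infection as a cause of raised CRP, and infection is one of the complications that lead to withdrawal. Strengths and limitations expects difficulties with adherence and digital skills, so such exclusions are foreseeable. Because no threshold is given and the staff who collect data know the allocation (Blinding), applying the rule also involves unblinded judgement.

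A patient removed before surgery may have no later CRP or WOMAC values. An analysis that promises to retain such patients would then have little to retain.

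**Working it through.** **Step 1: timing and arm of each clause.**

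| Clause under Enrollment | When it can occur | Which arm |
|---|---|---|
| Missed telerehabilitation sessions | After randomisation | Experimental only: controls have no sessions |
| No response on WhatsApp | After randomisation, once the programme runs | Experimental by strong inference: access is an entry condition for all, but contact is described only for this arm |
| Injury preventing home exercise | After randomisation | Worded for programme participants |
| Medical complication: stop the programme and withdraw | After randomisation | Worded mainly for programme participants, though such events also happen in controls |
| Surgery becomes contraindicated | After randomisation | Either arm |

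**Step 2: exclusion against retention.** A randomised experimental patient who stops attending sessions is excluded under Enrollment. The same patient is below 75%, and so is retained in the dose-response analysis under Prehabilitation adherence and in the analysis under Results. Both cannot be followed. The undefined degree of non-attendance under Enrollment also cannot be aligned with the 75% cutoff.

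**Step 3: illustration of size.** The documents give no figure for this bias.

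Inputs from Sample size: 78 × 1.10 = 85.8, rounded up to the stated 86; 86 / 2 = 43 expected per arm; CRP SD 10.95 mg/L from the cited study; overall attrition 10%.

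Assumptions not in the documents: no true effect; the least engaged share q of the experimental arm is removed; low engagement goes with higher CRP, correlation r = 0.3; one time point.

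With φ the standard normal density and z_q its q-quantile, the bias in SD units is r × φ(z_q) / (1 − q):

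- q = 0.10: 0.3 × 0.1755 / 0.90 = 0.058 SD; × 10.95 = 0.64 mg/L
- q = 0.20: 0.3 × 0.2800 / 0.80 = 0.105 SD; × 10.95 = 1.15 mg/L
- q = 0.40: 0.3 × 0.3863 / 0.60 = 0.193 SD; × 10.95 = 2.12 mg/L

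The standard error in SD units is √(1/(43(1 − q)) + 1/43) = 0.222, 0.229 and 0.249. With δ = bias / SE = 0.26, 0.46 and 0.78, the two-sided type I error Φ(δ − 1.96) + Φ(−δ − 1.96) is 5.8%, 7.4% and 12.1%. Simulated t-tests agree: about 6%, 7.5 to 8%, and 12%.

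With r = 0.1 and q = 0.20 the type I error is only 5.3%. With r = 0.5 and q = 0.20 it is 11.9%.

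**Step 4: the planned test.** Results specifies a group × time test over four CRP measurements. If engagement is related to CRP equally at every visit, the remaining experimental patients are shifted by the same amount at baseline and later, and the shift cancels in the change. Simulated change scores (r = 0.3 at each visit, within-patient correlation 0.5) show no bias and a type I error of about 5% at 10%, 20% and 40% removal. Bias in the planned test therefore needs engagement to predict change in CRP.

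**The case against.** The strongest counter-argument is that the exclusion paragraph may be a loosely worded per-protocol rule. The protocol has a per-protocol set at 75% and elsewhere states an intention to keep low adherers. The retention sentence under Prehabilitation adherence names only the dose-response analysis, and Results speaks of leaving the intervention whereas Enrollment speaks of leaving the study. The categories overlap rather than coincide. This softens the contradiction but does not remove it: the text says patients are excluded, not that they are left out of one analysis, and the non-attender in Step 2 is covered by both rules.

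Three stronger readings are tempting and are not supported:

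- *Every clause removes experimental patients only.* Loss of the surgical indication can happen in either arm, as can infections and cardiac events. One-sidedness is certain only for missed sessions.
- *Complications in withdrawn patients vanish from the 30-day outcomes.* Hospital outcomes are taken from medical records through the registration number, and nothing says that this review stops. Withdrawal from the study is stated only for patients with medical complications. Loss of CRP and WOMAC data is a risk, not a stated consequence for every excluded patient.
- *The primary test has a known, inflated type I error.* The figures in Step 3 describe a single-time-point comparison under an assumed correlation. At the plan's own 10% attrition, applied to the experimental arm, the inflation is small, and Step 4 shows that it can be absent from the planned test.

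**Conclusion.** The exclusion rule is wrong as written. Exclusion for non-attendance acts after randomisation on the experimental arm alone; exclusion for WhatsApp non-response very probably does too. The rule also conflicts with two statements that such patients are retained. This rests on the text and needs no numerical assumption.

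The amount of bias cannot be derived from the documents. Under the stated assumptions it runs from about 0.06 SD (10% removed) to 0.19 SD (40% removed) for a CRP comparison at one time point. It reaches the planned group × time test only if engagement predicts change in CRP. A later analysis plan can settle the analysis set, but it cannot restore measurements not taken because a patient was removed, so the correction belongs in the protocol.

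**What to change.** 1. Limit the exclusion criteria to conditions assessed before the envelope is opened.
2. Delete non-attendance and non-response as exclusions. Use adherence only to define the per-protocol set, at the existing 75% cutoff.
3. Separate stopping the exercise programme from leaving follow-up. The clinical decision to stop is left as it is.
4. Keep the scheduled blood draws, WOMAC and record review for all randomised patients who have not withdrawn consent, and analyse them in the arm allocated.
5. For patients who do not have surgery, keep the data that exist, report their number by arm, and treat post-TKA values as not available.
6. Reconcile the Enrollment paragraph with Prehabilitation adherence and the last paragraph of Results.

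The cost is mainly protocol wording. The visits and record review are already scheduled, so no new ones are needed. Some effort will go into keeping contact with patients who stop the programme.

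### Patients can be excluded after randomisation for missing telerehabilitation sessions, which only the experimental arm has; this conflicts with the stated retention of non-adherent participants

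*Protocol article*

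**What the plan says.** The exclusion rule is in the Enrollment subsection of Materials and methods: "Patients will be excluded if they fail to attend scheduled telerehabilitation sessions or respond to WhatsApp communication". The next sentences cover patients with unexpected medical complications, who "will be instructed to discontinue the program and withdraw from the study", and "new injuries during the prehabilitation period that prevented participation in home exercises".

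Under Randomization, "eligible participants who complete baseline assessments will be randomized using simple randomization with a 1:1 allocation ratio". Under Control group, "Participants in the control group will only follow these institutional procedures and will not engage in a home-based program". Under Experimental group, "weekly videoconference sessions provide real-time feedback, while WhatsApp monitoring facilitates communication"; the WhatsApp training and daily reminders also appear only there.

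Two later places treat non-adherence differently. Prehabilitation adherence sets a cut-off of 75% of prescribed sessions, uses it to decide who enters the per-protocol analyses, and adds that "all randomized participants will be retained in the dose-response analysis, regardless of adherence level". The last paragraph of Results describes a regression on dose-response, "including participants who did not reach the ≥75% adherence threshold" and those who withdrew from the intervention because of comorbidity or frailty, and says these people stay in the analysis.

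**The concern.** Poor attendance is something that happens after allocation. Used as a ground for exclusion from the trial, it lets behaviour under treatment decide who is compared. Controls have no sessions to miss, so the selection acts on one arm. Patients who miss calls or stop replying may well differ from the rest in frailty, comorbidity or motivation, and so in their recovery. Randomisation would then no longer protect the comparison of CRP, WOMAC or hospital outcomes.

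The article also gives staff two instructions that cannot both be followed: exclude the non-attender, and retain the non-attender. Which one is followed decides whether the later samples are taken and who is in the primary comparison.

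**Working it through.** **1. Timing.** Randomisation follows the baseline assessments. The sessions belong to the eight-week programme that starts after allocation, so nobody can miss one beforehand. The neighbouring exclusion sentences also concern events during the programme.

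**2. Which arm.** Controls receive the booklet and no programme, so the session half of the rule cannot apply to them. WhatsApp access is an entry requirement for everyone, but contact by WhatsApp is described only for the experimental arm. The WhatsApp half is therefore one-armed in all likelihood, though the article does not say so outright.

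**3. Contradiction, side by side.**

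| Place | What happens to a non-attender |
|---|---|
| Enrollment | excluded; no number of missed sessions given |
| Prehabilitation adherence | below 75%: outside the per-protocol set, kept in the dose-response analysis |
| Results, last paragraph | below 75%: kept in the analysis |

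The adherence definition tolerates some non-completion: 0.75 × 24 = 18 prescribed training sessions, so 6 may be missed. The exclusion rule states no tolerance of any kind.

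**4. Effect on the primary test.** Let q be the fraction of the experimental arm excluded, and δ(t) the mean CRP of excluded minus retained patients at time t.

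- Full-arm mean = retained mean + q × δ(t), so the retained mean differs from the full-arm mean by −q × δ(t).
- If excluded patients are dropped entirely, the change from baseline to time t is shifted by −q × [δ(t) − δ(0)].
- If δ is the same at every time point, the shift is 0 and the group-by-time interaction is unaffected.
- If δ grows after baseline, the shift favours the programme. For q = 8/43 = 0.186 and an assumed growth of 0.5 SD, it is 0.186 × 0.5 = 0.093 SD. The 0.5 SD is an assumption; the article gives no figure for it.

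Outcomes compared at a single time point (length of stay, complications, satisfaction) have no baseline value to cancel, so any stable difference would carry through in full.

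**5. Numbers of patients.** Inputs from Sample size: 78 required, 10% attrition, target 86.

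- Plan's figure: 78 × 1.10 = 85.8, rounded to 86 (78 / 0.90 = 86.7 would give 87; the gap is immaterial here).
- Allowance: 86 − 78 = 8 patients.
- Assuming an even split, 43 per arm: 8 / 43 = 18.6% of the experimental arm. Excluding that many gives 35 + 43 = 78 before any other loss.

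**The case against.** **The sentence may be a screening rule.** It stands under Enrollment, ahead of Randomization. This reading is weak: access to WhatsApp and availability for sessions are already separate inclusion criteria, and scheduled sessions exist only after allocation. The fix covers this case too.

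**The retention statements are narrow.** This stands. Both are tied to the dose-response regression, and neither expressly covers the primary CRP comparison. A reader might infer a promise to keep everyone in every analysis, which the article does not make. The conflict remains, because a patient excluded from the trial is not available for the dose-response analysis either.

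**Exclusion may not end data collection.** This stands in part. The article does not say that blood draws stop, and hospital outcomes come from medical records. Loss of the later samples is the ordinary meaning of exclusion, but it is an inference.

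Three stronger readings are tempting and are not supported:

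- *Most of the experimental arm would be excluded.* With an assumed 90% attendance per call, 0.9^8 = 0.43 would attend all eight weekly calls, so 57% would miss at least one. This needs zero tolerance, independent attendance and an attendance rate that the article does not give. Counting all 24 training sessions goes further astray: these are home sessions logged in a diary, and only the weekly calls are clearly scheduled remote contacts. For the same reason, a patient who completes 20 of 24 training sessions has not necessarily failed to attend a call.
- *The type I error can be quantified.* Simulating a single-time-point comparison (43 per arm, no true effect, 10% to 25% of the experimental arm removed, correlation of −0.2 to −0.5 between attendance and CRP) gives 5.2% to 15.5%, and about 5% at zero correlation. That is not the planned group-by-time test, into which a stable CRP difference would not carry.
- *The trial will fall below 78.* This depends on an exclusion rate that nobody has stated, and nothing says that such exclusions lie outside the 10% allowance.

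**Conclusion.** The concern holds on the text. The exclusion rule acts after randomisation; its session half can apply only to the experimental arm, and its WhatsApp half probably so. It has no threshold, and it cannot be reconciled with the retention of non-adherent participants in the adherence and missing-data paragraphs.

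The consequence is conditional. If excluded patients are dropped from follow-up or from the primary comparison, the between-arm results can be biased, probably in favour of the programme. The size is unknown. It may be zero for the group-by-time CRP test if excluded patients change after baseline as the others do. The only firm arithmetic is on numbers: with an even split, 8 exclusions among 43 experimental patients would use up the whole attrition allowance.

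This should be settled before patients are excluded under the rule, because samples that are not taken cannot be recovered by any later analysis.

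**What to change.** Delete the sentence from the exclusion criteria and state instead that:

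- missed sessions and unanswered messages count only as non-adherence, used for the per-protocol set;
- every randomised participant is invited to all remaining blood draws and visits;
- every randomised participant is analysed in the allocated arm in the primary comparison.

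If a pre-randomisation screen was intended (for example, whether the patient can join a video call), move it to eligibility and apply it to all candidates before the envelope is opened.

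The neighbouring sentences on medical complications and new injuries should be reconciled with the last paragraph of Results in the same way, by separating leaving the programme from leaving follow-up. When a patient should stop exercising is a clinical matter and is not addressed here.

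The cost is a short text change and slightly more follow-up work. The first two remaining draws fall the day before surgery and in the usual hospital stay, and a 30-day consultation is already planned. The estimated effect may be smaller, because non-attenders are included.

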In TKA, the extent of surgical trauma significantly influences postoperative pain and recovery. Plasma CRP, a well-established biomarker of tissue injury and inflammation, is commonly used to monitor recovery due to its rapid response, high specificity for acute inflammation, and ease of measurement, especially in elderly arthroplasty patients. CRP was selected as the primary outcome because of its association with osteoarthritis severity, surgical response, and postoperative complications, typically peaking on the third postoperative day [17].

Blood samples will be collected in an outpatient setting at four periods: before and after the eight-week prehabilitation program and three and 30 days post-TKA in both the experimental and control groups. The preoperative measurement one day before surgery (t3 in Figure 1) was timed to reflect chronic systemic adaptations resulting from prehabilitation while minimizing the confounding influence of acute exercise responses. This decision is supported by evidence showing that CRP typically returns to baseline (or a new post-exercise baseline) within six days after cessation of exercise [18]. The third postoperative day (t5) was selected to capture the peak inflammatory response following surgery, as supported by TKA-specific literature [17]. This time point also coincides with the typical hospitalization period, facilitating consistent, in-hospital sample collection. In the long term, given the anti-inflammatory effects of physical exercise, sustained reductions in CRP levels may reflect the effectiveness of the intervention in modulating systemic inflammation and promoting recovery [14].

Given that CRP levels can be influenced by factors such as sleep deprivation and acute infections, additional control measures will be implemented. Participants will report their average sleep duration and quality during the week preceding each blood draw (except for the third-day post-TKA measurement), as insufficient or disturbed sleep is associated with elevated CRP levels. Additionally, clinical symptoms suggestive of viral or bacterial infections (e.g., fever, sore throat, cough, or malaise) will be assessed before each collection since such conditions may increase CRP levels and confound the interpretation of the intervention's effects [19]. These precautions aimed to strengthen the internal validity of CRP as a primary outcome by minimizing interference from unrelated acute inflammatory processes.

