## Results

The significance level was set at p < 0.05, and analyses will be performed using IBM SPSS Statistics 21.0 (IBM®, Armonk, NY, USA). Data normality will be assessed using the Shapiro-Wilk test. Baseline demographic characteristics will be compared between the groups using independent t-tests (normal data), Mann-Whitney U tests (non-normal data), and chi-square or Fisher’s exact tests (categorical variables).

The primary outcome, changes in plasma CRP levels across four time points (nine weeks pre-TKA, one day pre-TKA, three days post-TKA, and 30 days post-TKA), and WOMAC scores across three time points (baseline, one day pre-TKA, and 30 days post-TKA) will be analyzed using two-way repeated-measures ANOVA (group × time interaction), contingent upon assumptions of normality and sphericity. If these assumptions are violated, linear mixed models (LMM) or generalized estimating equations (GEE) will be employed as more robust alternatives, capable of handling missing data and irregular intervals. Post-hoc pairwise comparisons will use the Bonferroni correction to adjust for type I errors. For non-parametric repeated measures, the Friedman test will be used, followed by Dunn-Bonferroni post-hoc tests when applicable.

Secondary outcomes, including synovial fluid and tissue biomarkers, hospital outcomes (length of stay, complications, readmissions), and satisfaction scores at specific time points, will be compared between groups using independent t-tests (normal data) or Mann-Whitney U tests (non-normal data). Correlations between biomarkers, hospital outcomes, WOMAC scores, and satisfaction will be examined using repeated measures correlation (rmcorr) for normal data or generalized linear mixed model (GLMM) for non-normal data. Rmcorr will be applied when assessing the strength and direction of associations between two continuous variables measured repeatedly within individuals. GLMM will be used in cases requiring the modeling of random effects, adjustment for covariates, or handling of non-normal or categorical outcomes, ensuring analytic flexibility across diverse data structures. To account for multiple comparisons in biomarker and exploratory analyses, false discovery rate (FDR) adjustment will be applied where appropriate.

Effect sizes (e.g., partial eta-squared for ANOVA and Cohen’s d for pairwise tests) and 95% confidence intervals will be reported alongside p-values to enhance the clinical interpretability of findings.

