## Conclusions

To the best of our knowledge, this is the first protocol for a two-arm, single-center randomized controlled trial comparing the effects of a home-based prehabilitation program versus a control condition on biomarkers and hospital outcomes in patients undergoing total TKA. By incorporating preoperative exercises with remote supervision, this approach aims to optimize biomarker profiles before and after surgery, enhance patient satisfaction, and improve self-reported pain, stiffness, and knee function, while potentially reducing hospital stay and postoperative complications. The findings from this trial will contribute to the growing evidence base for home-based prehabilitation and may inform future rehabilitation strategies and public healthcare policies aimed at improving TKA outcomes, particularly in overburdened systems with long surgical waitlists.

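### The protocol contradicts itself on where the day-3 CRP sample is drawn; if it is drawn in hospital only, patients discharged earlier could lack the value and be deleted from the first-line primary analysis

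*Protocol article*

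**What the plan says.** All references are to the protocol article.

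- **Primary outcome, setting of the draws:** "Blood samples will be collected in an outpatient setting at four periods: before and after the eight-week prehabilitation program and three and 30 days post-TKA". Day 3 is named among the outpatient draws.
- **Primary outcome, same paragraph, reason for day 3:** "The third postoperative day (t5) was selected to capture the peak inflammatory response following surgery", followed by "This time point also coincides with the typical hospitalization period, facilitating consistent, in-hospital sample collection".
- **Hospital outcomes:** length of stay is a trial outcome, and "reduced length of stay may reflect improved physiological readiness for discharge".
- **Conclusions:** the programme is described as improving recovery "while potentially reducing hospital stay and postoperative complications".
- **Results (analysis methods):** CRP over the four time points "will be analyzed using two-way repeated-measures ANOVA (group × time interaction), contingent upon assumptions of normality and sphericity". The alternative is conditional: "If these assumptions are violated, linear mixed models (LMM) or generalized estimating equations (GEE) will be employed as more robust alternatives".
- **Results, last paragraph:** the missing-data statement covers low adherence and withdrawal from the intervention. It does not address a missed blood draw.

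**The concern.** CRP is the primary outcome, and day 3 is the time point chosen to catch its peak. A site reading the Primary outcome section cannot tell whether a patient who has gone home by day 3 should be called back or recorded as missing. The Blinding section says data collectors know the allocation, so an unclear rule could also be applied differently in the two arms.

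Under the in-hospital reading, having a day-3 value requires still being an inpatient on day 3. Length of stay is something the programme might shorten, so availability of the primary outcome would depend on another outcome that may differ by arm. Repeated-measures ANOVA needs all four values. A patient missing only day 3 would therefore also lose the baseline, preoperative and day-30 values. If early-discharged patients tend to have lower CRP, and more of them are in the experimental arm, the remaining experimental patients look worse than the arm as a whole.

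**Working it through.** **1. The contradiction.** The setting sentence says outpatient for all four draws, day 3 included. The rationale sentence says day 3 suits in-hospital collection. Neither says what happens to a patient discharged earlier.

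**2. What happens to a missing value.** ANOVA is first-line and uses complete cases. The switch to a linear mixed model or GEE depends on normality and sphericity. The text notes that these methods can handle missing data, but missing data do not trigger the switch.

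**3. Size of the possible bias.** The plan gives no figure for length of stay or for day-3 missingness, so there is none to reproduce. The only CRP scale is in Sample size: a difference of 9.12 mg/L and a pooled SD of 10.95, which reproduces the stated d: 9.12 / 10.95 = 0.83. The article does not say at which time point that SD applies, so the mg/L values below are for scale only.

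Assumptions, not from the documents:
- sampling is in hospital only;
- a share p of each arm is discharged before the draw;
- standardised day-3 CRP is normal, with correlation r = 0.2 to 0.6 between low CRP and the tendency to early discharge.

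The mean shift among those still sampled is r × φ(z) / (1 − p), with z = Φ⁻¹(1 − p). The bias is the experimental shift minus the control shift.

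For p = 0.10: φ(1.2816) / 0.90 = 0.1755 / 0.90 = 0.195. For p = 0.20: φ(0.8416) / 0.80 = 0.2800 / 0.80 = 0.350. The difference is 0.155, so the bias is 0.155 × 0.2 = 0.031 SD to 0.155 × 0.6 = 0.093 SD.

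| Discharged before draw, control / experimental | Bias, SD (r = 0.2 to 0.6) | Bias, mg/L (× 10.95) |
|---|---|---|
| 5% / 10% | 0.017 to 0.052 | 0.2 to 0.6 |
| 10% / 20% | 0.031 to 0.093 | 0.3 to 1.0 |
| 20% / 40% | 0.059 to 0.176 | 0.6 to 1.9 |
| equal shares, or outpatient draw for all discharged | 0 | 0 |

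The sign is against the experimental arm. At 10% / 20%, 0.3 to 1.0 mg/L is roughly 4% to 11% of the quoted 9.12 mg/L (0.34 / 9.12 and 1.02 / 9.12).

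**4. Cross-check by a simpler model.** If early-discharged patients have CRP lower by D SD than those who stay, the bias is D × (experimental share − control share). With D = 0.5 to 0.83 and 20% versus 10%, that is 0.05 to 0.083 SD, in the same range.

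**5. Patients lost.** With 39 per arm and 10% / 20%: 39 × 0.10 + 39 × 0.20 = 11.7 of 78, or 15%. The attrition allowance is 86 − 78 = 8 patients, for all causes.

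**6. Power.** The correlation among repeated measures is not stated, so the 78 cannot be confirmed. At an assumed correlation of 0.5, with 86 × 0.9 = 77.4 patients reduced by a further 10% or 20%, power of a between-group test at f = 0.25 goes from 78% to 74% or 69%. Power of the planned group × time interaction stays above 99%. Power is therefore not the main argument.

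**The case against.** A reader might infer that patients discharged early will drop out of the primary analysis unequally by arm. The documents do not support that as a stated consequence. It would need in-hospital-only sampling, a material number discharged before day 3, more of them in the experimental arm, and lower CRP in those patients; the loss from all time points also needs ANOVA to be the method used. None of these is established:

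- The only statement on timing places day 3 within the typical stay, which suggests that early discharge may be uncommon. The 20% / 40% row sits badly with it.
- Hospital outcomes and Conclusions speak of shorter stay only as something that may or potentially could follow.
- No section links CRP to discharge timing, so the range for r is pure assumption.
- The in-hospital sentence is a rationale for choosing day 3. It can be read alongside the outpatient sentence: in hospital if still admitted, otherwise as an outpatient.
- CRP across a surgical peak may well fail normality or sphericity, in which case the mixed model might be used anyway.

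Most of this stands, and it limits the point to a conditional risk. Two things remain. The text does not state the combined reading, so the contradiction is there to be resolved. Reliance on the mixed model is also left to chance: its use depends on a test of assumptions, and the same paragraph offers the Friedman test for non-parametric repeated measures, which likewise needs complete data.

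**Conclusion.** The point holds as an internal contradiction about where the peak sample of the primary outcome is drawn, with a conditional risk of unequal loss attached. Under the in-hospital-only reading, with assumed early discharge of 10% versus 20% and r of 0.2 to 0.6, the bias is about 0.03 to 0.09 SD, or 0.3 to 1.0 mg/L at SD 10.95, against the experimental arm. With equal early-discharge shares, or if discharged patients are sampled as outpatients, it is zero. The true size cannot be known from the documents. The correction is still worthwhile, because it is cheap and a missed day-3 sample cannot be recovered later.

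**What to change.** 1. **Primary outcome:** replace the two sentences with one rule for both arms. The t5 sample is taken on postoperative day 3 in every operated participant, in hospital if still admitted and otherwise at the outpatient draw already named.
2. **Results:** make the linear mixed model, already named as an alternative, the primary CRP analysis from the outset, so that a participant missing one sample keeps the others. The model does not fully correct loss that depends on the unobserved day-3 value itself, so the sampling rule is the more important change.
3. **Reporting:** give, by arm, the number of participants without a day-3 value.

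A sample taken at discharge should not stand in for day 3. It would be a pre-peak value and, if early discharge were commoner in the experimental arm, could bias the comparison the other way. Nothing here calls for a rule on when patients are discharged.

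The cost is a wording change in two places and an early return visit for any participant discharged before day 3, which the outpatient sentence already implies.
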